#### d. Selectivity of the mechanism to target tissue in animals and/or human beings

See SPC page 6

#### e. Analysis of potential effect

See SPC page 5 and 6

#### f. Pharmacokinetic considerations

See SPC page 7, 8 and 9

#### g. Study population

Healthy male subjects aged > 40 years either lean (BMI < 24 kg/m^2) or obese (BMI > 28 kg/m^2)

#### h. Interaction with other products

See SPC page 4 and 5

#### i. Predictability of effect

In our retrospective study, 88% of the subjects using metformin had a high F-FDG-uptake in the colon.

#### j. Can effects be managed?

The change of a lactate acidosis is very small since subjects should be healthy (e.g. no lactate acidosis in medical history, no medication use) and kidney function will be checked. However, when subjects show symptoms of lactate acidosis (acidotic dyspnoe,

abdominal pain and hypothermia) subjects should call the study doctor and contact their general practitioner.

## 11.2 Synthesis

Metformin is a widely used drug with an established safety profile. The most-occurring side-effect is gastrointestinal discomfort (diarrhoea, bloating, dyspepsia). This is mostly seen at high doses and often ameliorates when using metformin for a longer period. A rare but important complication is lactic acidosis. However, this is most often seen in patients with either renal insufficiency or other underlying causes of impaired lactate metabolism. Therefore, we only include healthy subjects and kidney function will be checked before subjects start with the metformin.

Furthermore, we will use  $^{18}\text{F}$ -FDG PET-CT scans to evaluate the glucose uptake in the intestine. The resulting dose from the two radioactive tracers + scans is 7.8 mSv.

The maximal dose for a participant during one year is 10 mSv. Nonetheless, we will strongly emphasize that the participants will not participate in research involving radiation in the two years following this study. Although the change of developing cancer is minimal after participation in this study, we will only include subjects aged over 40 years to minimize the potential effect of inducing cancer.

Last, the placing of the intravenous cannula in our study can be a unpleasant experience for the subjects and there is a low risk of flebitis at the intravenous injection sites.

Although the methods of our study are accompanied with a moderate risk for healthy subjects, we find this to be justified with adding knowledge to finding a solution for the major obesity and type 2 diabetes epidemic.

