There is no direct benefit for the volunteers. The resulting dose from the radioactive tracers + the scans is 7.8 mSv. The placement of an intravenous canula can be an unpleasant experience and there is a small chance of developing flebitis at the site of the intravenous canula. While using metformin, the subjects can encounter side effects of the metformin. This research will provide insight into the working mechanism of metformin and its potential role in the treatment of obesity.

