#### Study visits and procedures

During the **first** study visit, participants will come to the AMC for screening to determine eligibility for the study. During this visit, informed consent will be obtained after oral and written explanation of the study. Subsequently, length, weight, waist circumference and medical history will be acquired. In total, a maximum of 20 ml of blood will be drawn to perform laboratory measurements needed to determine eligibility for the study (kidney function and liver function). The chronic use of drugs and/or medication will be asked at the participant. If eligible, the second visit will be scheduled.

The **second and third visit** are similar. Core body temperature will be measured using a body core pill and tympanic temperature will be measured every 15 minutes. Blood will be drawn to measure insulin sensitivity, in total 40 ml of blood will be drawn to be able to perform blood tests and as stored serum. After 60 minutes an energy expenditure (EE) will be performed using indirect calorimetry. Glucose uptake in the colon will be evaluated using  $^{18}\text{F}$ -FDG PET CT.

After the **second** visit, subjects will receive the metformin and information on how to use this.

**Flow chart;** overview of the procedures that subjects will undergo in the course of the study.

[figure not shown]

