#### 4.2 Inclusion criteria

- Male
- Caucasian origin
- Subjects should be able and willing to give informed consent
- > 50 years old
- BMI< 24 kg/m^2 or > 28 kg/m^2

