#### 4.3 Exclusion criteria

- Renal failure (GFR< 60ml/min)
- Liver insufficiency (AST or ALT 3 times upper value)
- Chronic use of drugs or medication
- Diabetes mellitus
- Lactate acidosis or precoma diabeticum in medical history
- Acute or chronic diseases such as: dehydration, severe infection, shock, heartfailure, pulmonary insufficiency, recent heart attack
- Alcoholism

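### Section 11.2 cites a one-year maximum of 10 mSv without saying what it counts, and no visible eligibility or screening item asks about earlier radiation research

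*Protocol*

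**What the plan says.** Section 11.2 of the protocol gives the radiation burden: "The resulting dose from the two radioactive tracers + scans is 7.8 mSv". The Summary gives the same figure: "The resulting dose from the radioactive tracers + the scans is 7.8 mSv". Section 11.2 then names a yearly ceiling, "The maximal dose for a participant during one year is 10 mSv", and goes on to say the team will stress that "participants will not participate in research involving radiation in the two years following this study". It does not define what the ceiling counts.

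The eligibility rules are in 4.2 and 4.3. Section 4.2 covers sex, origin, consent, age and BMI. Section 4.3 covers renal and liver function, chronic drug or medication use, diabetes, a history of lactate acidosis or diabetic precoma, acute or chronic disease, and alcoholism. Neither list mentions earlier radiation or earlier research participation.

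The screening visit in section 3 consists of consent, body measurements, a general medical history and blood tests of kidney and liver function. It names one specific history question: "The chronic use of drugs and/or medication will be asked at the participant". After that, "If eligible, the second visit will be scheduled". Section 7.2 adds vital signs and lists the invasive procedures, and it too has no question on earlier radiation.

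**The concern.** A ceiling expressed per participant and per year may be meant to cover more than one study. If so, the order of the studies does not matter: a dose received two months before entry counts as much as one received two months after the last scan. The protocol addresses only later participation, and that only as something to be emphasised to volunteers. Earlier participation is what the team can check before giving any dose, and the visible text does not check it.

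Other safeguards in 11.2 do have a counterpart in the criteria. The kidney-function check appears as a GFR limit in 4.3, and the minimum age intended to limit cancer risk is matched by an age criterion in 4.2. Earlier radiation has none.

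Participant protection is at stake. These are healthy volunteers who, according to the Summary, have no direct benefit. On one reading of 11.2, staff who follow 4.2 and 4.3 exactly could enrol a man whose yearly total goes above the figure the protocol itself cites.

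**Working it through.** **Inputs**

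- Study dose for both PET-CT scans: 7.8 mSv (section 11.2; same figure in the Summary).
- Cited one-year maximum: 10 mSv (section 11.2), scope not stated.
- Counted dose from other sources in the same year: x mSv. The protocol gives no value, so x is an assumption throughout.

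**Check of the plan's own figure.** The 7.8 mSv agrees between the Summary and 11.2. It cannot be rebuilt, because the protocol gives neither the injected activity nor the CT dose. It is taken as stated.

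**Headroom.** 10 - 7.8 = 2.2 mSv. The study uses 7.8 / 10 = 78% of the cited maximum and leaves 22%.

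**Reading A: the 10 mSv counts other research exposure.** Total = 7.8 + x, which exceeds 10 only if x > 2.2.

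| Assumed x (mSv) | Total (mSv) | Above 10? |
|---|---|---|
| 0 | 7.8 | no |
| 1 | 8.8 | no |
| 2.2 | 10.0 | no (at the limit) |
| 3.9 (one scan like those here, if 7.8 splits equally) | 11.7 | yes |
| 7.8 (a study like this one) | 15.6 | yes |

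**Reading B: the 10 mSv only benchmarks this study's dose.** Total = 7.8, below 10 for every participant whatever his history.

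**Would the criteria stop a man with x > 2.2 from earlier research?** Take a healthy man who meets the sex, origin, age and BMI criteria, uses no medication, and recently took part in another radiation study. He meets every item in 4.2. None of the exclusions in 4.3 applies to him; the disease item, for example, reads "Acute or chronic diseases such as: dehydration, severe infection, shock, heartfailure, pulmonary insufficiency, recent heart attack". The medical history might bring out the earlier study, but 4.3 would give the investigator no ground to exclude him. The second visit would be scheduled.

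**The case against.** The strongest counter-argument is that 11.2 does not establish reading A. The sentence about later research opens with a word of contrast, which suggests the authors regarded 7.8 mSv as within the 10 mSv figure and added the restriction as an extra precaution. The periods also differ: one year for the maximum, two years for the restriction. The restriction therefore does not simply apply the 10 mSv limit, and it is weak evidence of what that limit counts. Section 11.2 is a risk synthesis, and it does not undertake to keep each man's yearly total below 10 mSv. All of this stands. A reader might infer that the protocol contradicts its own dose limit. The text does not support that, because the contradiction appears only once a scope is assumed.

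A second argument is that some of the gap may be covered elsewhere. A medical history is taken, and healthy men without acute or chronic disease are less likely to have had recent diagnostic or therapeutic radiation. The flow chart in section 3 is not visible in the text reviewed, and the information letter mentioned in 10.2 is a separate document, so a question could sit in either. This stands in part: the absence of a screening item is firm only for the visible text. But good health says little about earlier research participation, and neither the flow chart nor the letter would replace a criterion in 4.3.

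A third argument is that the size of the problem is unknown. That is correct. A reader might infer from the table that exceeding 10 mSv is likely; the protocol gives neither an earlier dose nor a rate of earlier participation, so no such statement can be made.

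**Conclusion.** The point holds as a conditional one. Two things are certain from the visible text: 11.2 leaves the scope of the 10 mSv open, and no eligibility, screening or procedure item covers radiation research before entry. If the maximum counts other research exposure, a man with more than 2.2 mSv from another study in the same year can be enrolled under the criteria as written and exceed it. If it only benchmarks the study's own dose, nothing is exceeded. The documents do not decide between these readings.

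The conclusion rests on the protocol's own 7.8 and 10 mSv, neither of which is disputed here. How often the case would occur cannot be estimated. The matter concerns who is enrolled and how they are protected; the endpoints and the analysis are not affected. The severity is the lowest: a cheap improvement to consider.

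**What to change.** 1. Add to 4.3 an exclusion for participation in other research involving radiation in the 12 months before the first PET-CT or during the study. Together with the existing request about the two years afterwards, this covers research exposure in any 12-month period that contains a study scan. Excluding on participation is more practical than a 2.2 mSv cut-off, which a volunteer is unlikely to be able to report.
2. Ask about it at the screening visit (section 3), with a brief reconfirmation before the first scan.
3. Have the sponsor state in 11.2 what the 10 mSv counts. The scope is for the sponsor to decide. If medical exposure is meant to count as well, the question and the criterion should be widened to match.

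The cost is one exclusion line, one question asked twice, and one clarifying sentence. The drawback is that an occasional volunteer will be deferred or excluded on a self-reported history.
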